# **Study Completion, Discontinuation, or Interruption**

## **Study Completion**

　Upon completion at each site, the investigator will submit the study completion report to the hospital director. In multicenter trials, a report will also be submitted to the study representative.

## **Discontinuation or Interruption of the Study**

　The principal investigator will review continuation of the study if:

1) Significant information on study drug quality, safety, or efficacy is obtained.

2) Recruitment difficulties make it impossible to achieve the target number of subjects.

3) The study objective is achieved before reaching the planned sample size or period (e.g., via interim analysis).

4) If the Data and Safety Monitoring Committee (DSMC) issues instructions to modify the protocol or other aspects of the trial, and it is judged difficult to comply with such instructions, the trial may be discontinued.

In addition, if the DSMC recommends or instructs termination, the trial will be stopped. For multicenter trials, the principal investigator or the committee specified in the protocol shall review the above matters and determine whether the trial should continue.
 When a decision is made to discontinue or interrupt the trial, the hospital director must be promptly notified in writing with the reasons.

# **Endpoints**

## **Primary Endpoint**

　Relapse-Free Survival (RFS)

【Rationale】

Although the true endpoint to evaluate treatment efficacy is overall survival (OS), this trial is an exploratory phase II study to examine the significance of extensive intraperitoneal lavage for the target cases. It is desirable that results be obtained early. Therefore, RFS, which is an important surrogate endpoint for OS, was set as the primary endpoint.

【Definition of Recurrence】

　Recurrence is defined as follows (definitions of measurable and non-measurable lesions follow RECIST^10^:

1. Detection of any new measurable lesion on postoperative follow-up CT, defined as:
2. Tumor lesion: maximum diameter ≥ 10 mm　② Lymph node lesion: short axis ≥ 15 mm
3. Presence of non-measurable lesions as described below, along with tumor marker levels exceeding the upper limit of normal at the institution.

*Non-measurable lesions:* Small lesions (tumor lesions with long axis < 10 mm or lymph nodes with short axis ≥ 10 mm and < 15 mm), and all lesions other than measurable lesions, including true non-measurable lesions. True non-measurable lesions include leptomeningeal disease, ascites, pleural or pericardial effusion, inflammatory breast cancer, lymphangitic spread in skin or lungs, and abdominal masses or organ enlargement detectable by palpation but not reproducible by imaging.

RFS is defined as the number of days from surgery to either meeting the above criteria for relapse or death.

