# **Background**

The mortality rate of gastric cancer in Japan has continued to decline in both men and women since the 1970s, and in men, lung cancer surpassed gastric cancer as the leading cause of cancer-related death after 1993; however, gastric cancer remains the second leading cause of death from malignant neoplasms in Japan¹. According to the Japanese Gastric Cancer Treatment Guidelines (3rd edition), standard surgery for tumors with N(+) involvement or T2 or deeper is either distal gastrectomy or total gastrectomy. Total gastrectomy is indicated when an adequate resection margin cannot be secured by distal gastrectomy. Regarding lymph node dissection for advanced gastric cancer, based on the results of the JCOG9501 trial conducted in Japan, D2 lymphadenectomy is considered the standard treatment. Concerning adjuvant therapy after curative resection, based on the results of the ACTS-GC trial (Adjuvant Chemotherapy Trial of S-1 for Gastric Cancer), postoperative administration of S-1 for one year has become the standard treatment in Japan for patients with stage II–IIIB gastric cancer (excluding pT1)². Furthermore, following the results of the randomized phase III trial (CLASSIC trial) comparing surgery alone with adjuvant chemotherapy using capecitabine plus oxaliplatin (CapeOX), CapeOX therapy is also recommended as a postoperative adjuvant chemotherapy option³.
 These treatment developments have improved the survival outcomes of patients undergoing gastric cancer surgery. However, even after curative resection, peritoneal recurrence has been reported in 37–39.4% of cases (JCOG9206-1, JCOG9206-2, JCOG9501 trials). In all these trials, the most common site of recurrence after curative resection was the peritoneum. In the ACTS-GC trial, peritoneal recurrence occurred in 14.6% (77/549) of patients even with adjuvant chemotherapy⁴. These findings indicate that even among cases currently judged as curatively resected by staging, there are high-risk patients for peritoneal dissemination recurrence.
 At present, peritoneal cytology (CY) is the most widely used method to predict peritoneal dissemination recurrence. The 5-year overall survival rate for CY-positive cases has been reported to be approximately 0–2%, indicating an extremely poor prognosis. This highlights the need for novel treatment development to improve outcomes in this patient population^⁵,⁶^.

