**8-2-3 Postoperative Assessment Items**

1) Pathological findings

􀂂 Histological type of primary lesion

􀂂 Depth of invasion, lymph node metastasis

􀂂 Proximal and distal margins

􀂂 Histopathological stage, overall curability

􀂂 Details of each lymph node metastasis

2) Recurrence status

􀂂 Regular follow-up as described below will be conducted to assess recurrence by the attending physician or study office. Recurrence sites will also be recorded.

- 1. Tumor markers (CEA, CA19-9): every 3 months for 3 years postoperatively
  2. CT of upper abdomen and pelvis: every 6 months for 3 years postoperatively
  3. Upper gastrointestinal endoscopy: once a year only for distal gastrectomy

Schedule Table

| Item | Pre-op | Post-op Observation Period | | | | | | | | | | | |
| --- | --- | --- | --- | --- | --- | --- | --- | --- | --- | --- | --- | --- | --- |
| Time | 2–4 weeks before | 3M | 6M | 9M | 1Y | 1Y  3M | 1Y  6M | 1Y  9M | 2Y | 2Y  3M | 2Y  6M | 2Y  9M | 3Y |
| Consent acquisition | ● |  |  |  |  |  |  |  |  |  |  |  |  |
| Patient background | ● |  |  |  |  |  |  |  |  |  |  |  |  |
| Subjective/objective symptoms | ● | ● | ● | ● | ● | ● | ● | ● | ● | ● | ● | ● | ● |
| Adverse events observation ^a^ |  | ● | ● | ● | ● | ● | ● | ● | ● | ● | ● | ● | ● |
| Upper GI endoscopy | ● |  |  |  | ● |  |  |  | ● |  |  |  | ● |
| CT scan | ● |  | ● |  | ● |  | ● |  | ● |  | ● |  | ● |
| Hematology tests ^b^ | ● | ● | ● | ● | ● | ● | ● | ● | ● | ● | ● | ● | ● |
| Biochemistry tests ^c^ | ● | ● | ● | ● | ● | ● | ● | ● | ● | ● | ● | ● | ● |
| Physiological function tests | ● |  |  |  |  |  |  |  |  |  |  |  |  |

M: Month、Y: Year

a: Adverse events include all undesirable events, regardless of causality with the drug.

b: Hematology tests include WBC, hemoglobin, platelet count; used to confirm safety.

c: Biochemistry tests include TP, albumin, AST, ALT, total bilirubin, creatinine, CRP, CEA, CA19-9; used to confirm safety and treatment effect.

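### The RFS definition gives proven recurrence no route of its own: if it is not measurable on CT and markers are normal, the event is dated late, and the comparison with 0.86 years may be biased

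*Protocol*

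**What the plan says.** Section 11.1 (Primary Endpoint) of the protocol gives two routes to recurrence.

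- Route 1 is radiological: "Detection of any new measurable lesion on postoperative follow-up CT, defined as", with the limits "Tumor lesion: maximum diameter ≥ 10 mm ② Lymph node lesion: short axis ≥ 15 mm".
- Route 2 needs two findings together: "Presence of non-measurable lesions as described below, along with tumor marker levels exceeding the upper limit of normal at the institution".

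Non-measurable covers tumour lesions under 10 mm, nodes of 10 to under 15 mm short axis, and every other lesion that is not measurable. The section adds: "True non-measurable lesions include leptomeningeal disease, ascites, pleural or pericardial effusion", and also masses that can be felt but not reproduced on imaging.

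The endpoint is tied to this list: "RFS is defined as the number of days from surgery to either meeting the above criteria for relapse or death".

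Section 8-2-3 has the attending physician or the study office assess recurrence. It schedules CEA and CA19-9 every 3 months and CT every 6 months for 3 years, and endoscopy as follows: "Upper gastrointestinal endoscopy: once a year only for distal gastrectomy". It adds no further criterion for recurrence. The Background, citing earlier surgical trials, says that "the most common site of recurrence after curative resection was the peritoneum".

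Section 13.2 declares success if the lower 90% confidence limit for RFS exceeds 0.86 years. Sections 6.1 and 6.2 take that figure from the department's own patients operated on from 1997 to 2012 (138 patients, median 315 days). They do not say how recurrence was defined or dated in that series.

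**The concern.** The list in section 11.1 is closed, and neither route accepts tissue, cytological, endoscopic or operative proof by itself. Malignant ascites confirmed by cytology, small peritoneal deposits seen at operation, or an anastomotic recurrence biopsied at the scheduled endoscopy is not an event if CT shows nothing measurable and CEA and CA19-9 are normal. Cytology makes a patient eligible for this trial, yet positive cytology later on does not establish a relapse.

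The population is chosen for its risk of peritoneal recurrence, and ascites and small deposits are the findings that the definition makes conditional on a marker. Late dating therefore falls mainly on the recurrence that the intervention is meant to prevent. The trial has one arm and is judged against a fixed number, so no concurrent control carries the same delay. If the historical series dated relapse more promptly, the delay would count as benefit.

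The protocol states this definition in full, so it is not a detail left for a statistical analysis plan.

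**Working it through.** **The plan's own figure.** The sample size is not in dispute and reproduces. With one-sided α = 0.05 (which matches the 90% interval), 80% power, and medians of 0.86 and 1.2 years:

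- events = (1.645 + 0.842)² / [ln(0.86/1.2)]² = 55.7
- P(event) under the alternative, with 2 years' accrual and 3 further years of follow-up: λ₁ = ln 2 / 1.2 = 0.578, so P = 1 − (e^(−3λ₁) − e^(−5λ₁)) / (2λ₁) = 0.895
- N = 55.7 / 0.895 = 62.2, against the stated 62

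The 315-day median cannot be checked from the protocol.

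**Effect of late dating when lavage does nothing.** From the protocol: threshold 0.86 years, n = 65, 90% interval. Assumed, because the protocol gives neither: the share *f* of all RFS events that are dated late, and the delay δ. The values 0.25 and 0.5 years for δ match the marker and CT intervals in section 8-2-3. True RFS is taken as exponential with median 0.86 years, so λ = ln 2 / 0.86 = 0.806.

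*Success rule.* With no censoring before 0.86 years, the Kaplan-Meier rule (log-log interval) passes when at least 40 of 65 patients are event-free at that time. With 40 the lower limit for the proportion is 0.508; with 39 it is 0.493. With no delay, P(Binomial(65, 0.5) ≥ 40) = 4.1%.

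*Full delay.* Recorded RFS at 0.86 years is p = (1 − f)·0.5 + f·0.5^((0.86 − δ)/0.86). The last power is 0.612 for δ = 0.25 and 0.748 for δ = 0.5.

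*Delay ended by death.* Under section 11.1 death is an event, so it cuts the delay short. Assume a median of 6 months from relapse to death, so μ = ln 2 / 0.5 = 1.386. For an affected patient the proportion still recorded event-free at 0.86 years is 0.5 + 0.5·λ·(1 − e^(−(μ − λ)δ)) / (μ − λ). This is 0.594 for δ = 0.25 and 0.675 for δ = 0.5.

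| f | δ (years) | p, full delay | False success | p, death ends delay | False success |
|---|---|---|---|---|---|
| 0 | – | 0.500 | 4.1% | 0.500 | 4.1% |
| 5% | 0.25 | 0.506 | 4.9% | 0.505 | 4.8% |
| 5% | 0.5 | 0.512 | 6.2% | 0.509 | 5.5% |
| 10% | 0.25 | 0.511 | 5.9% | 0.509 | 5.6% |
| 10% | 0.5 | 0.525 | 9.0% | 0.517 | 7.2% |
| 20% | 0.25 | 0.522 | 8.4% | 0.519 | 7.5% |
| 20% | 0.5 | 0.550 | 17.4% | 0.535 | 12.0% |

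A simulation of the full-delay case with staggered entry and a 90% log-log interval for the Kaplan-Meier median agrees: about 4% with no delay, 6% or 9% at f = 10%, and 8% or 16% at f = 20%. The recorded median moves from 0.86 to 0.89 or 0.92 years at f = 10%, and to 0.91 or 0.98 years at f = 20%.

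These figures apply to the comparison only if the historical series did not carry the same delay.

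**The case against.** Four points can be made for the plan.

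1. A reader might infer that such recurrences are missed. Mostly they are not. The event counts once a lesion becomes measurable, a marker rises or the patient dies, and only censoring before then loses it. Proven disease that is measurable, or that comes with a raised marker, counts at once. This stands, and the point is late dating.

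2. A reader might infer that RFS is shown to be inflated against 0.86 years. It is not. The threshold comes from the department's own patients; if recurrence there was dated by the same rule, this bias does not arise. The protocol's silence supports stating and aligning the definition, not a claim of proven bias. This stands.

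3. The marker condition has an evident purpose: it keeps non-specific fluid or tiny nodules from being called relapse. Dropping it for unproven lesions would put the attending physician's judgement in place of an objective rule in a single-arm trial. This stands. Route 2 can also err the other way, because it asks neither that the lesion be new nor that it be shown malignant. Benign ascites or an effusion with a raised marker would count and shorten RFS. Section 8-2-2 itself lists pleural effusion and chylous ascites among postoperative complications.

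4. The percentages rest on assumed shares and delays. This stands too, and at a 5% share the effect is slight.

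None of this supplies a route for recurrence that has been proven but is neither measurable nor marker-positive.

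**Conclusion.** The point holds as a gap in the primary endpoint definition. Followed as written, section 11.1 dates recurrence with pathological or operative proof late whenever it is not measurable on CT and markers are normal. This lengthens RFS relative to actual relapse, mainly for peritoneal disease. Whether it also favours the intervention against 0.86 years depends on how the 1997–2012 series dated recurrence, which the protocol does not state. If that series used clinical or pathological diagnosis, it does.

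In that case, and with no true effect, false success rises from about 4% to 5–9% for a 5–10% share delayed 3–6 months. For a 20% share it rises to 8–17%, or to about 7.5–12% if death at an assumed median of 6 months after relapse ends the delay. Every share, every delay and the post-relapse survival are assumptions. The calculation also leaves out the opposite error from benign fluid with a raised marker.

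A reader might further infer that the secondary endpoint on recurrence sites under-counts the peritoneum. That is not shown. Section 8-2-3 has sites recorded, and a peritoneal relapse dated late is still recorded as peritoneal. A site could be lost only through death or censoring before the criteria are met.

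**What to change.** Amend section 11.1 so that cytological, histological, endoscopic-biopsy or operative confirmation of recurrence is sufficient whatever the marker levels, dated at confirmation. Keep the marker condition for non-measurable lesions without such proof.

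State in section 6.1 or 6.2 how recurrence was defined and dated for the 138 historical patients. Re-derive the 0.86-year threshold with the amended definition, as far as the records allow, and carry any change through to the sample size in section 6.2 and the success rule in section 13.2. Report RFS under the current definition as a sensitivity analysis.

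The cost is a change of wording, a re-read of historical records, and a threshold that may move. Older records may not allow every relapse to be re-dated; where they do not, the report should say so.

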## **Inclusion Criteria**

1) Histologically confirmed gastric cancer by endoscopic biopsy (pap, tub1, tub2, por1, por2, sig, muc, or special types).

2) Positive peritoneal cytology or imprint cytology, no other distant metastasis, and R0/1 resection feasible via D2 gastrectomy (total or distal, including laparoscopic), under general ± epidural anesthesia.

3) Esophageal invasion ≤3 cm; no thoracotomy required.

4) Age 20–80 years.

5) ECOG PS 0–1.

6) No prior chemotherapy (including endocrine therapy) or radiotherapy for other cancers.

7) All of the following criteria must be met. (The latest preoperative laboratory values within 56 days before enrollment will be used. Tests performed on the same day of the week 8 weeks prior to enrollment are acceptable.)

① White blood cell count: 3,000–10,000/mm³

② Platelet count ≥100,000/mm³

③ AST ≤100 IU/L, ALT ≤100 IU/L

④ Total bilirubin ≤2.0 mg/dL

⑤ Serum creatinine ≤1.5 mg/dL

8) Written informed consent for study participation has been obtained from the patient.

［Rationale］

1) To ensure that the case is histologically confirmed as gastric cancer.

2) Patients with positive peritoneal cytology or imprint cytology are considered high-risk for peritoneal recurrence and are therefore eligible. However, patients with other distant metastases are often unable to achieve R0/1 resection and are excluded from this study.

3) Patients with esophageal invasion ≥3 cm may require thoracotomy and are excluded.

4 -7) Special cases or patients with poor preoperative general condition are excluded.

8) Patient consent is mandatory.

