# **Study Design**

## **Type and Design**

This is a single-arm, non-randomized phase II study to evaluate the superiority of extensive intraoperative peritoneal lavage for recurrence-free survival in patients undergoing D2 gastrectomy with positive intraoperative peritoneal or imprint cytology. For setting the threshold, survival outcomes of 138 eligible patients operated at our department from 1997 to 2012 were used.

**Rationale:** The target population is rare, and patient accrual may require considerable time. Therefore, a randomized controlled trial is considered difficult, and this single-arm phase II study uses historical outcomes to set thresholds.

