## **Clinical Hypothesis and Sample Size Determination**

1. **Clinical Hypothesis:**

Extensive intraoperative peritoneal lavage may prolong recurrence-free survival in patients with positive intraoperative peritoneal or imprint cytology after D2 gastrectomy.

1. **Sample Size Determination:**

The median recurrence-free survival of CY- or imprint-positive patients operated at our hospital from 1997 to 2012 was 315 days (0.86 years). This value was set as the threshold, and the expected median RFS with the study intervention is 438 days (1.2 years). Assuming α=0.05 and β=0.20, 62 patients are required. The planned enrollment is 65 patients.

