## **Efficacy Analysis**

Prior to describing the analysis method, the analysis population is defined. Patients registered according to Section 5.1, excluding duplicate or misregistered cases, constitute the "All Registered Patients." Excluding ineligible patients defines the "All Eligible Patients," which is the analysis population.
 The trial treatment will be judged effective if the lower bound of the 90% confidence interval for RFS in all eligible patients exceeds the threshold of 0.86 years.

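### Section 11.1 does not count relapse proven by histology or cytology when markers are normal and CT shows no measurable lesion, so such relapses enter RFS late or not at all

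*Protocol*

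**What the plan says.** Section 11.1 (Primary Endpoint, Definition of Recurrence) gives two routes to relapse. The first is a new measurable lesion on postoperative CT: a tumor of at least 10 mm, or a node with a short axis of at least 15 mm. The second is "Presence of non-measurable lesions as described below, along with tumor marker levels exceeding the upper limit of normal at the institution". The list of what is non-measurable is wide: "True non-measurable lesions include leptomeningeal disease, ascites, pleural or pericardial effusion" and, in general, anything that is not measurable. The endpoint is then closed: "RFS is defined as the number of days from surgery to either meeting the above criteria for relapse or death".

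The inclusion rationale in section 4.1 names the form of relapse the trial is aimed at: "Patients with positive peritoneal cytology or imprint cytology are considered high-risk for peritoneal recurrence and are therefore eligible".

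Section 8-2-3 schedules tumor markers every 3 months and "CT of upper abdomen and pelvis: every 6 months for 3 years postoperatively". Endoscopy is yearly, for distal gastrectomy only, first at 1 year. The attending physician or study office assesses recurrence, but the section adds no criterion of its own.

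The threshold is historical (section 6.1): "survival outcomes of 138 eligible patients operated at our department from 1997 to 2012 were used". Section 13.2 judges the treatment effective if the "lower bound of the 90% confidence interval for RFS in all eligible patients exceeds the threshold of 0.86 years".

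**The concern.** Neither route gives any standing to pathology. If a biopsy or a fluid sample proves recurrence while CEA and CA19-9 are normal and CT shows nothing measurable, section 11.1 followed literally records no event. The patient stays relapse-free on paper until a measurable lesion appears, a marker exceeds normal, or death.

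This reaches the relapse of main interest. Ascites is classed as non-measurable, so even cytology-positive ascites needs a raised marker to count. Positive cytology is enough to enter the trial but not to establish relapse.

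The error has one direction. Compared with a definition that accepts pathological proof, events can only be delayed or lost, and observed RFS can only lengthen. In a single-arm trial judged against a fixed threshold there is no concurrent arm to absorb such a shift. What counts as a primary event is fixed in the protocol, so an analysis plan could not close the gap without contradicting section 11.1.

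**Working it through.** **1. Is there another route in the document?** Section 11.1 has two routes plus death. Section 8-2-3 says who assesses recurrence, not by what further standard. No other section supplies a pathology criterion. The list numbering in section 11.1 is disturbed, but nothing suggests a lost third route.

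**2. The plan's sample size, for reference.** With medians 0.86 and 1.2 years, HR = 0.86/1.2 = 0.717. Events = (1.645 + 0.842)² / (ln 0.717)² = 55.7. With exponential RFS, 2 years of uniform accrual and 3 more years of follow-up, P(event) = 0.895, so N = 55.7/0.895 = 62.2, against the stated 62 (one-sided 5%). The gap does not touch this figure, and the fix does not change it.

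**3. When can the gap change the decision?** Sections 6.2 and 13.2 are read together as a rule on the median. The lower 90% limit for the median exceeds 315 days when the lower 90% limit for S(315) exceeds 0.5. Only relapses that occur before day 315 and are still uncounted on day 315 can matter. Scheduled endoscopy begins at 1 year, after day 315, and no postoperative biopsy or ascites cytology is scheduled. That leaves unscheduled sampling before day 315.

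**4. Illustration of size.** Assumptions not in the document:
- N = 65 with no censoring before day 315
- a log-log interval
- exponential RFS with a true median of 315 days when all relapses count
- a threshold that did count these relapses
- a share q = 2–10% of relapses of this kind

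Baseline: the lower limit of S(315) is 0.493 at 39/65 and 0.508 at 40/65, so success needs X ≥ 40 patients event-free at day 315. For X ~ Bin(65, 0.5), P(X ≥ 40) = 0.041.

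With the gap, S_obs(315) = 0.5 + q·f, where f is the fraction relapsing before day 315 but counted after it, and S(t) = 2^(−t/315).

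| Counted at | f | Patients crossing day 315 (65·q·f) | False-positive risk, q = 2% to 10% |
|---|---|---|---|
| next 3-month marker visit (days 274, 365) | S(274) − 0.5 = 0.047 | 0.06 to 0.31 | 4.2% to 4.8% |
| next 6-monthly CT (days 183, 365) | S(183) − 0.5 = 0.1685 | 0.22 to 1.10 | 4.6% to 7.1% |
| 183 days late in every case | S(132) − 0.5 = 0.248 | 0.32 to 1.61 | 4.8% to 9.0% |

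With counting at the next CT, the risk reaches 5.0% at q = 3.5%.

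**5. Sensitivity to the interval.** With a plain-scale 90% interval the lower limit at 39/65 is 0.50005. Success then needs X ≥ 39, and the baseline risk is P(X ≥ 39) = 6.8% with no gap at all. The choice of interval alone moves the risk about as far as the next-CT row at q = 10%.

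**6. Effect on the estimated median.** A case found at the 1-year endoscopy and counted at 1 year 6 months can move the estimate. With an exponential median of 438 days, S(t) = 0.5 − 1/65 at t = 457.7 days, a shift of 19.7 days for one case. This changes the reported median, not the day-315 decision.

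**The case against.** **The case is narrow.** Three things must hold together: no measurable CT lesion, a normal marker, and pathological proof. Section 11.1 names no particular marker and does not ask for a new rise, so a non-measurable lesion with one raised marker plausibly counts already. Markers are checked every 3 months. This stands, and it limits the size.

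**The share is assumed.** Nothing in the document supports 2–10%. The share that matters is smaller than the share of all such relapses, because those found at scheduled endoscopy come too late to affect day 315. This also stands; the table shows direction and rough scale only.

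**A fixed CT-and-marker rule is defensible.** It limits variation between sites in a multicenter trial. That is a fair reason for such a rule, but not for setting aside a relapse that has been proven.

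**The added criterion could itself create a mismatch.** If the historical patients were scored by the current rule and cannot be re-scored, the trial would count events that the benchmark did not. It would also depend partly on who happens to be sampled. This is a real cost and shapes the fix.

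A reader might go further and infer that the comparison is biased in favour of lavage, or that the false-positive risk is materially inflated. The document does not support either inference. It does not say how relapse was defined in the 138 historical patients, and if the same rule applied there, this source of bias largely cancels.

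**Conclusion.** The gap in section 11.1 is real. Relapse proven by histology or cytology, with normal markers and no CT-measurable lesion, is not an RFS event until a CT-measurable lesion, a marker above normal or death. A lesion below the measurable size on a later CT does not close the gap, because it still needs a raised marker.

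The direction is certain and the size is not. The effect on the 0.86-year decision is probably small: fewer than two patients in every scenario above, under an assumed share and an assumed interval. Whether it biases the trial against its threshold depends on the unstated historical definition. The point is worth acting on because it concerns the primary endpoint, runs in one direction and is cheap to correct; the success rule is not shown to fail.

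**What to change.** Add a criterion to section 11.1: *Recurrence confirmed by histology or cytology at any site, whatever the tumor marker level; the event date is the date of sampling.*

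Check how relapse was defined in the 138 historical patients, and apply the same definition to them when setting the threshold. If their records do not allow this, report RFS under the current section 11.1 definition as a sensitivity analysis, so that any mismatch with the 0.86-year threshold is visible.

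Cost: one sentence in the protocol and, where records allow, a chart review of the historical patients. There is no added procedure or visit, since only pathology obtained in usual follow-up is used, and the planned sample size is unchanged. The downsides are a possible small mismatch with the historical threshold and some dependence on discretionary sampling.
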